**APPENDIX D: Vaccine Tolerability Assessment Form**

Please describe how much discomfort you experienced at three different points in the procedure. For each timepoint, circle the word that best describes the discomfort you felt:

**1. When the device was placed on your skin and the vaccine was injected, *before* the electrical stimulation**

0 1 2 3 4 5

*none light uncomfortable intense severe excruciating*

**2. Immediately *after* the electrical stimulation and muscle contraction**

0 1 2 3 4 5

*none light uncomfortable intense severe excruciating*

**3. Thirty minutes after the vaccination was completed**

0 1 2 3 4 5

*none light uncomfortable intense severe excruciating*

In your opinion, would this procedure be acceptable if it protected people from getting a serious disease (such as HIV / AIDS) for which we currently do not have a vaccine?

***Yes No Not Sure***

In your opinion, would this procedure be acceptable if it was able to provide significantly improved protection against a serious disease (such as influenza) for which we already have a vaccine?***Yes No Not Sure***

**Additional Comments or feedback, if any:**

**___________________________________________________________________________________________**

**___________________________________________________________________________________________**

Initials: __________ Date: ___________________

**APPENDIX D: Volunteer Diary Card**

**Volunteer Diary Card**

**Protocol DHO-0614-0707**

Volunteer ID Number

Date and time of injection

Date of Next Visit:

Name of Study Contact:

24 HOUR EMERGENCY telephone number to report any unusual or severe symptoms that occur before the next visit:

** Please bring this card to your next clinic visit.

If you experience any symptoms following this vaccination that persist beyond day 3 (72 hours) please indicate the severity for each one noted in the column under the day you noticed the symptom. Unless an item says MEASURE, please rate severity as “-“for none, “+” for mild, “++” for moderate, or “+++” for severe.

| **Code** | **Meaning** |
| --- | --- |
| - | Symptom not present |
| + | Mild: Transient or mild discomfort, no limitation in normal daily activity |
| ++ | Moderate: Some limitation in normal daily activity |
| +++ | Severe: Unable to perform normal daily activity |

| **Possible Symptoms** | **Date** | **Date** | **Date** | **Date** | **Date** | **Date** | **Date** |
| --- | --- | --- | --- | --- | --- | --- | --- |
| Local Symptoms  Pain (pain without area being touched) at injection site |  |  |  |  |  |  |  |
| Tenderness (pain when area being touched) at injection site |  |  |  |  |  |  |  |
| Redness (erythema) at injection site  MEASURE | mm | mm | mm | mm | mm | mm | mm |
| Skin damage (vesicles, ulcers) at injection site  MEASURE | mm | mm | mm | mm | mm | mm | mm |
| Hardness or thickening (induration) at injection site MEASURE | mm | mm | mm | mm | mm | mm | mm |
| Swelling (edema) at injection site |  |  |  |  |  |  |  |
| Formation of crust, scab or scar MEASURE | mm | mm | mm | mm | mm | mm | mm |
| Systemic Symptoms  Headache |  |  |  |  |  |  |  |
| Chills |  |  |  |  |  |  |  |
| Nausea |  |  |  |  |  |  |  |
| Vomiting |  |  |  |  |  |  |  |
| Temperature MEASURE  Measure before midnight of the date stated | °F | °F | °F | °F | °F | °F | °F |
| Feeling of general discomfort, uneasiness, a general sick feeling (malaise) |  |  |  |  |  |  |  |
| Muscle aches (myalgia) |  |  |  |  |  |  |  |
| Aching joints (arthralgia) |  |  |  |  |  |  |  |

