- Review interim medical history (including concomitant medications)
- Review safety laboratory data
- Review the informed consent form administered at screening visit with volunteer
- Perform a directed physical examination including vital signs (pulse, respiratory rate, blood pressure and temperature) as well as an assessment of axillary lymph nodes and any further examination indicated by history or observation
- Conduct pre HIV-test counseling
- Perform a skin-fold measurement of the upper arm (Appendix B)
- Collect blood and urine specimens for all tests as indicated in the Schedule of Procedures (Appendix A)
- Perform a pregnancy test for all female volunteers (blood will be sent stat)and obtain results prior to vaccination
- Perform baseline assessment of the site of injection and evaluate and record any systemic symptoms
- Administer vaccine (the preferred site of administration is the deltoid muscle of the upper arm) either by standard intramuscular injection or by electroporation. Depending upon the amount of adipose tissue at injection site, the length and gauge of the standard intramuscular needle and the gauge of the electroporation device will be adjusted (Appendix B)

Volunteers will be closely observed for at least 30 – 45 minutes after vaccination. Vital signs (pulse, respiratory rate, blood pressure and temperature) will be monitored at 30 – 45 minutes after vaccination and recorded. Any local and systemic reactogenicity events, as well as any other event that occurs, will be recorded at 30 – 45 minutes. At this time, subjects will also be asked to complete a Vaccine Tolerability Assessment Form (Appendix D). Furthermore, volunteers will be given a diary card (Appendix E) and asked to record any reactogenicity events that occur between Day 1 and Day 7 and Day 57 and Day 64, as well as Day 253 and Day 260 in those volunteers in the high dose EP group who elect to receive a third vaccination. Site staff will explain to the volunteer how to record reactogenicity events.

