### Human trials with DNA vaccines

Several studies have been performed in humans with DNA vaccines other than HIV.DNA vaccines. Anti-malaria DNA vaccines administered intramuscularly induced some CTL and no antibody responses, and were well tolerated up to 2.5 mg per dose.15,16 A pilot study (Protocol 400-003-03) with an HIV env/rev DNA construct was conducted in HIV-uninfected volunteers at the National Institutes of Health (NIH) Clinical Centre, USA. Doses as high as 3 mg were given as a single injection. Adverse events were mild and infrequent and T-cell responses were observed.17

A Phase 1 clinical study (AVEG Protocol 031) with an HIV-1 gag/pol DNA vaccine was performed in 52 HIV-1 uninfected adult volunteers aged 18-60 years with low risk for HIV-1 infection. Doses as high as 3 mg at 0, 1, 3 and 6 months were given. This vaccine was able to induce antigen-specific proliferation and production of chemokines by PBMC of vaccinated individuals, *in vitro*. Preliminary data on this HIV-1 gag-pol DNA vaccine were presented by Tellez et al. 18

In early 2000, Merck began a human trial of a DNA vaccine using HIV gag with the intention to boost with recombinant adenovirus. Preliminary data have been presented documenting safety and immunogenicity (Emini, CROI IX, Seattle, Washington, 2002).

A candidate DNA.HIVA vaccine has undergone Phase 1 clinical trials through the collaboration of IAVI, the Medical Research Council in Oxford, UK and with the Kenya Aids Vaccine Initiative (KAVI) in Nairobi, Kenya. The DNA.HIVA vaccine was given to a total of 31 volunteers at either 100µg (n=6) or 500 µg (n=25) intramuscularly. It has been well tolerated and immunogenic. Local side effects observed in the UK trial were mild to moderate, occurred mostly on the first post-vaccination day and resolved by 48 hours. Systemic side effects were mild to moderate and resolved within 1-3 days. In the Kenya trial no local or systemic side effects have been observed. A Phase 1 study testing a prime-boost approach and enrolling 120 volunteers started at the beginning of April 2002 in the UK. Dosage levels up to 2 mg DNA. HIVA per injection are being tested. As of May 19, 2003, approximately 103 individuals have been enrolled. No pattern of risk has been found among reported events. Thus far the vaccine has been found to be generally safe and well tolerated.

Human Trials with ADARC Vaccines

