**d) Primary Endpoints**

**Safety and Tolerability**:

- Severe local reactogenicity events (pain, tenderness, erythema/skin discoloration, edema, damage [vesiculation/ulceration], induration, formation of a crust or scab.
- Severe systemic reactogenicity events (fever, chills, headache, nausea, vomiting, malaise, myalgia, arthralgia, rash).
- Severe other adverse events (including laboratory abnormalities).
- All Serious Adverse Events.
- Proportion of volunteers with mild and moderate local and systemic reactogenicity events.
- Electroporation Tolerability Assessment Questionnaire Responses (Appendix B)

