5. The application of electroporation will result in a brief, localized muscle contraction at the site of administration, which may be painful. Approximately 10% of subjects may experience a tingling sensation in their arm and fingers after administration. Since intramuscular DNA delivery with electroporation results in increased intracellular uptake of plasmid at the site of injection and electric field application, the procedure may increase the frequency and/or severity of local site reactions. Such symptoms should not last longer than several days. However, volunteers will be removed from the study if injection reactions ≥ Grade 3 in severity occur
6. We do not know what effect the vaccine would have on an unborn child if given to a pregnant woman. Females of childbearing potential will be advised to use a reliable form of contraception, as discussed with a nurse counselor, until study completion. A pregnancy test will be performed at screening, on the day of vaccination, and at every visit throughout the course of the fourteen-month study. Males who are not anatomically sterile (those who have had a vasectomy or medically proven to be sterile)should use condoms until study completion to avoid pregnancy in a spouse or partner
7. Following vaccination a participant may become HIV positive on a routine HIV test. This test result does not mean that person has HIV or AIDS. It could mean that exposure to the vaccine resulted in the production of antibodies to it. In case of a positive HIV test result, an independent laboratory will confirm whether the positive test is the result of the vaccination or whether the participant contracted HIV through exposure in the community. In the event that an individual has a vaccine-induced positive serology, ADARC will provide documentation of that individual’s participation in this vaccine trial
8. It is unknown whether receiving this HIV vaccine will alter the immune response to any future HIV vaccine that may be developed in the future
9. The possibility of integration of the DNA plasmid vector into genomic DNA of transfected myocytes has been considered. Plasmid integration at a sufficiently high frequency carries the possibility of inducing deleterious gene expression modifying mutations (e.g. inactivation of a tumor suppressor gene). Potential side effects could include an increased risk of malignancy arising from the cells harboring the mutation(s).

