**How to Measure Thickening and Redness and skin damage**

Check for hardness or thickening (induration), redness (erythema) and skin damage (vesicles, ulcers) at injection site on Day 1, 2 and 3 after each injection. (Day 1, 2 and 3 are 24, 48, and 72 hours after study vaccination respectively).

If you see any thickening, redness, or lump at the injection site, use the measuring tape provided to measure the WIDEST part of the response on Days 1, 2, and 3.

Record the result rounded to the *nearest 10*, for example, 0, 10, 20, or 30.

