**Directions for Oral Temperature**

You will be given a supply of 3M Tempa-DOT Disposable Thermometers to use for recording your temperature on Day 1, 2 and 3 after each vaccination.

1. Wait at least 15 minutes before taking your temperature after exposure to cold weather, smoking, eating or drinking.
2. Place thermometer under tongue as far back as possible with dots facing either up or down.
3. Press tongue down on thermometer and keep mouth closed for 60 seconds.
4. Remove thermometer. Wait 10 seconds. Some dots may disappear as device locks in for accuracy.
5. Read the last blue dot. Ignore any skipped dot. Record temperature on the diary card.

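### The diary card asks volunteers to grade symptoms only if they outlast 72 hours, contradicting the protocol body and risking under-recording of short-lived reactogenicity in the primary safety endpoints

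*Protocol*

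**What the plan says.** The protocol gives more than one rule for what the diary card collects.

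- **Vaccination Visits section:** volunteers receive the card and are "asked to record any reactogenicity events that occur between Day 1 and Day 7 and Day 57 and Day 64", with a matching window after the optional third vaccination. No persistence condition is attached.
- **Volunteer Diary Card, general instruction:** "If you experience any symptoms following this vaccination that persist beyond day 3 (72 hours) please indicate the severity for each one noted". The table below it has seven date columns, a code for an absent symptom, and a mild code whose definition includes transient discomfort.
- **Card, measurement instructions:** for thickening, redness or a lump, "use the measuring tape provided to measure the WIDEST part of the response on Days 1, 2, and 3". Skin damage is also to be checked on those days.
- **Card, temperature instructions:** thermometers are supplied "to use for recording your temperature on Day 1, 2 and 3 after each vaccination".

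The endpoints these data feed are in section d) Primary Endpoints. They include "Severe local reactogenicity events (pain, tenderness, erythema/skin discoloration, edema, damage" and further local signs, severe systemic events, and "Proportion of volunteers with mild and moderate local and systemic reactogenicity events". None has a minimum duration. Rash is among the listed systemic events.

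**The concern.** Reactogenicity is part of the primary safety result, and the card is the only daily record of it. If volunteers follow its general instruction, reactions that come and go within three days are not graded on the card.

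The protocol's own text suggests that many reactions will be short. Under Risks and Alternative Methods it says of local reactions to electroporation: "Such symptoms should not last longer than several days". In its background on an earlier intramuscular DNA vaccine, local effects "occurred mostly on the first post-vaccination day and resolved by 48 hours" and systemic effects resolved within one to three days.

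Three things are at stake. The proportions with mild and moderate reactions could be too low. Grades could be wrong, because Appendix C grades pain and several systemic symptoms on limitation of activity and on single versus repeated analgesic doses, details that fade in recall. And volunteers who follow different instructions would give data that are not comparable, in groups of 8 where one misclassified volunteer moves a proportion by 1/8 = 12.5 percentage points. The DSMB, which receives adverse events of grade 2 or higher before approving escalation, would see the same data.

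**Working it through.** The plan has no figure on this point to reproduce. Its only precision figures (0.37, 0.21 and 0.14) concern vaccine-related SAEs and do not depend on the diary. The check is therefore a reconciliation of texts, followed by an illustration.

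**1. Which items does the 72-hour condition reach?**

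- With a separate Day 1–3 instruction: redness, induration, skin damage, temperature.
- With no separate instruction, so governed only by the general sentence: pain, tenderness, swelling, crust or scab (marked for measurement in the table but absent from the measuring instructions), headache, chills, nausea, vomiting, malaise, myalgia, arthralgia.
- With no row at all: rash.

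No item is instructed as the Vaccination Visits section requires, that is, any event throughout Days 1–7. The first group of items has explicit instructions for Days 1–3 but not for Days 4–7, although the table has cells for seven dates. The second has an instruction only for symptoms lasting beyond Day 3.

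**2. What else captures a reaction that resolves within 72 hours?**

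- Staff record reactogenicity 30–45 minutes after each vaccination (Vaccination Visits).
- Staff telephone once, 1 to 4 days after each vaccination (Post-Vaccination Visits; shown as D3, D59 and D255 in Appendix A).
- The first four electroporation recipients in each dose group get an additional call the day after vaccination.
- Staff assess reactogenicity at the Week 1 visit and at the matching visits after later doses, by which time a short reaction is a matter of recall.

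**3. How large could the loss be?** Let p be the true proportion with a reaction, q the share of reactions lasting beyond 72 hours, and r the share of shorter reactions recovered by telephone or clinic. Then

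observed proportion = p × [q + (1 − q) × r].

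The protocol gives none of the three, so all are assumptions. Take p = 0.75 in a group of 8 (6 true reactors) and q from 0.10 to 0.50. For example, with q = 0.10 and r = 0.5: 8 × 0.75 × (0.10 + 0.90 × 0.5) = 6 × 0.55 = 3.3.

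| r | q = 0.10 | q = 0.50 |
|---|---|---|
| 0 | 0.6 | 3.0 |
| 0.5 | 3.3 | 4.5 |
| 0.9 | 5.5 | 5.7 |
| 1 | 6.0 | 6.0 |

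The entries are expected numbers of recorded reactors out of 8. The direction is the same throughout. The size runs from a large loss to none and is driven mainly by r.

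**4. Window lengths.** Week 8 is Day 56 and Week 36 is Day 252, so Days 57–64 and 253–260 are post-dose Days 1–8, against Days 1–7 after the first dose. An eight-day window does not fit a seven-column card. This is a small inconsistency.

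**The case against.** The strongest reply is that the card is neither wholly restricted nor the only source. Redness, induration, skin damage and temperature are requested on Days 1–3 without any persistence condition. Staff explain the card to each volunteer, and its seven columns and mild code suggest that daily recording from the start was intended. The sentence may have been meant as a request to continue beyond Day 3, although it does not say so. No endpoint is defined by the diary alone, and the staff contacts listed above all collect reactogenicity. The analysis is descriptive and exploratory.

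Most of this stands, and it rules out several stronger readings.

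- A reader might infer that the card records nothing before 72 hours. That is untrue of the four items with Day 1–3 instructions.
- A reader might infer that the endpoints will miss short reactions, so that a group with 6 of 8 reactors would be reported as 0 of 8. That ignores every staff contact, and no figure in the protocol supports near-total loss.
- A reader might infer that a late Week 36 dose would leave almost no diary days, because Days 253–260 are fixed study days. The card has an injection date field and blank date columns, and it counts its days from vaccination, so it follows the actual dose.
- The short durations quoted from the background belong to a different vaccine given without electroporation. They make short reactions plausible here but do not establish how long these will last.

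What the reply does not remove is the contradiction itself. The 30–45 minute check is too early for later-onset symptoms, the routine call may come as early as the day after vaccination, the additional next-day call covers only the first four electroporation recipients per dose group, and Week 1 relies on memory. Verbal explanation by staff may correct the printed sentence or repeat it; the protocol does not say which.

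**Conclusion.** The point holds in limited form. The card's general instruction contradicts the Vaccination Visits section and fits poorly with the card's own mild code and date columns. For the eleven items without a Day 1–3 instruction, reactions resolving within 72 hours may be under-recorded or mis-graded, which biases the primary reactogenicity proportions toward fewer events. The loss cannot be fixed from the protocol: on the assumed inputs it runs from nearly all reactors to none, depending on recovery by telephone and clinic. The conclusion rests on at least some volunteers following the printed sentence and some reactions being short. The Day 1–3 limit on measurements and temperature, the missing rash row and the unequal windows are real but minor. None of this undermines the design, but daily data that were never collected cannot be restored at analysis.

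**What to change.** - Remove the 72-hour persistence condition from the card.
- Ask for every listed item, including temperature and measured signs, on each of post-vaccination Days 1–7, counted from the actual injection date and identical for every vaccination, with the absent code entered where there is no symptom.
- Add a row for rash.
- Align the Vaccination Visits section with the card's general, measurement and temperature instructions, including the seven- versus eight-day windows.
- State which source (card, telephone or clinic) determines the endpoint grade when they differ.
- Correct the label: the Vaccination Visits section calls the card Appendix E, but it is headed Appendix D.

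The cost is a wording amendment, a reprinted card and a few more thermometers per volunteer. No visit or sample size changes.

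### The diary card never asks for each symptom's worst severity on every day, nor for the day's peak temperature, so maximum reactogenicity grade may be under-recorded

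*Protocol*

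**What the plan says.** The Volunteer Diary Card (Protocol, Appendix D) has 15 symptom rows and seven date columns. Ten rows are graded by the volunteer: pain, tenderness, swelling, headache, chills, nausea, vomiting, malaise, myalgia and arthralgia. Five are measured: redness, skin damage, induration, crust/scab/scar and temperature. The rating rule is "please indicate the severity for each one noted in the column under the day you noticed the symptom". The codes run from a dash, defined as "Symptom not present", to three plus signs for severe.

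The temperature row adds "Measure before midnight of the date stated". The directions for oral temperature supply thermometers for "recording your temperature on Day 1, 2 and 3 after each vaccination". The measuring instructions ask for hardness, redness and skin damage to be checked on those same three days.

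The rating sentence opens with a condition: "If you experience any symptoms following this vaccination that persist beyond day 3 (72 hours"). The Vaccination Visits section instead asks for any reactogenicity event over roughly the week after each dose.

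The primary endpoints (section d) include "Severe local reactogenicity events", their systemic counterpart, and "Proportion of volunteers with mild and moderate local and systemic reactogenicity events".

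**The concern.** Endpoints that sort volunteers into mild, moderate and severe need the highest grade reached. The card does not ask for it. If a volunteer enters headache or arm pain once, on the day it is first noticed, and it worsens the next day, the entry stays at the lower grade. Fever carries a smaller risk of a different kind: the reading is repeated on three days, but the one value per date may not be that day's highest.

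Both errors run in one direction. An onset grade or an arbitrary-time temperature cannot exceed the peak, so severe reactions would be under-counted and lower grades over-counted. If volunteers read the instruction differently, the endpoint is also measured inconsistently between them. The boundary between moderate and severe is used elsewhere too: enrolment pacing after the first four electroporation volunteers in a dose group turns on whether any event exceeded moderate, and the suspension rule counts related severe events. A peak that was never written down cannot be restored at analysis.

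**Working it through.** The protocol states no figure on this point, so the check is mainly a comparison of its texts.

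**Graded symptoms (10 rows).** The rating sentence on the card is the only written instruction.

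- Read as onset only: 1 of 7 cells is filled per symptom.
- Read as a daily grid: up to 7 of 7 cells are filled.
- For the second reading: there are seven dated columns and a code for an absent symptom, and a symptom that lasts three days can be said to be noticed on three days.
- For the first reading: the sentence speaks of the day, in the singular. Where the card wants repetition, as for temperature, redness, hardness and skin damage, it says so and names Days 1, 2 and 3. It gives no such order for the graded rows.
- Under either reading, nothing asks for the worst severity of the day or of the episode.

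The text does not settle which reading applies.

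**Measured items.** Temperature and the named skin checks are repeated on Days 1, 2 and 3, so onset-only recording does not arise for them on those days. The instruction to measure the widest part of a skin reaction concerns its extent on the skin, not its peak over time. Temperature has one cell per date, to be filled at any time before midnight, with no request for the highest value or for a reading when feverish. In Appendix C moderate fever spans 38.7 to 39.3 °C, a band of 39.3 − 38.7 = 0.6 °C, so the time of the reading can change the grade.

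**Other sources of severity.**

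| Contact | Where stated | Does it supply daily peaks? |
| --- | --- | --- |
| Check 30–45 minutes after the dose | Vaccination Visits | No, first hour only |
| Phone call 1 to 4 days after the dose | Post-Vaccination Visits | Once, partway through |
| Extra next-day call, first four electroporation volunteers per dose group | Safety Review Plan | Day 1 only, for these volunteers |
| Week 1 visit, with card returned and reactogenicity assessed | Post-Vaccination Visits | By recall |
| Questioning and/or examination at each visit, severity by Appendix C | Adverse Event Definition; Assessment of Severity | By recall |

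None of these provisions tells staff to obtain the peak for each day.

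**Illustration only.** Assume 10% of volunteers truly reach a severe reaction. Let q be the share of them whose severe grade comes on a later day than the one entered. Assume also that everyone rates at onset only and that staff recover nothing. The recorded rate is p = 0.10 × (1 − q). The chance that a group of n shows at least one severe reaction is 1 − (1 − p)^n.

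| q | p | n = 8 (one dose group) | n = 24 (all ADVAX/EP) |
| --- | --- | --- | --- |
| 0 | 0.100 | 0.570 | 0.920 |
| 0.25 | 0.075 | 0.464 | 0.846 |
| 0.50 | 0.050 | 0.337 | 0.708 |

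Neither the 10% nor any value of q comes from the protocol. For a given q the table shows the largest possible loss, because daily raters and staff contacts would both reduce it.

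**The case against.** The strongest reply is that the grid itself asks for daily rating. Seven dated columns and a code for absence would have little purpose if each symptom were entered once, and the rating sentence contains no word such as first or onset. Staff explain the card in person, telephone, assess reactogenicity at Week 1, question volunteers at every visit and grade against Appendix C. The card also carries a 24-hour number for severe symptoms. Nowhere does the protocol say that the endpoint comes from the diary alone.

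Most of this stands, and it limits the point. A reader might infer that the card calls for one rating per symptom, so that later worsening is lost and severe reactions are recorded at their onset grade. The documents do not support that. The wording permits the single entry but does not require it, the layout points the other way, and a reaction that becomes severe on Day 3 can still be graded severe at a call or visit. Nor does fever share an onset-only flaw, since temperature is repeated daily on Days 1 to 3. It would also go too far to say that a blank cell can never be told from an absent symptom: the card defines a code for absence, though it does not say that the code must be entered on every symptom-free day.

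What the reply does not remove is the gap in the written instruction. If daily rating was intended, the card does not say so. The spoken explanation has no stated content that would fill the gap, and the later contacts rely on memory.

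**Conclusion.** The point holds in limited form. The card does not tell volunteers to rate each graded symptom every day at that day's worst severity, and it does not direct the temperature reading to the day's peak. Maximum grade may therefore be under-recorded, and recorded differently by volunteers who all comply. Any resulting bias is downward for severity. Its size cannot be derived from the protocol: it depends on how many volunteers enter a symptom once, how often the peak comes later, and how much staff recover. None of these is given, so the illustrative probabilities are not estimates. The change is worth making because these are primary endpoints in groups of eight, where one misgraded severe reaction alters the observed proportion by 1/8 = 12.5 percentage points.

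The 72-hour condition at the start of the same sentence is a separate contradiction with the Vaccination Visits section and with the card's own Day 1 to 3 instructions. Removing it would leave the present gap in place.

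**What to change.** Replace the rating instruction with: *Every day, for every item, enter the worst severity since your last entry; enter the dash code if the symptom was absent.* Replace the temperature note with: *Record the highest temperature of the day, with an extra reading if you feel feverish.* Have staff use the same wording when they explain the card.

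The cost is two sentences on the card and slightly more writing for volunteers: 15 items a day over seven dates, or 15 × 7 = 105 cells per vaccination. No visit, staff time or procedure is added beyond an occasional extra thermometer reading.

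Separately, reconcile the 72-hour condition with the diary period in the Vaccination Visits section and with the card's Day 1 to 3 measuring and temperature directions, so that all of them describe the same days and the same events.
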